#### Rationale & background information

The use of tumor necrosis factor-alpha (TNF-α) blockers for the treatment of patients with psoriasis increases the risk of developing tuberculosis (TB) in 25-fold compared to those who do not receive these medications (SOLOVIC, 2013). Therefore, current consensuses advocate screening for latent tuberculosis infection (TBLI) with a tuberculin skin test (TST) before initiating the use of TNF-α blocking drugs (DAUDEN et al., 2016; CONSENSO…, 2012; COMISSÃO..., 2009; GRUPO..., 2002)

However, the application of TST in patients with psoriasis presents many problems. On one hand, there are reports of tests with false-negative results, being questioned whether these would be due to immunosuppression, energy, or technical errors. In these cases, patients were allowed to use TNF-α blockers and may develop Latent Tuberculosis infection (LTBI) (FORTALEZA et al, 2008; GOUJON et al., 2010; SHAIKHA et al., 2012; ABREU et al., 2013; YOO et al., 2014). On the other hand, TT has a higher frequency of positive and strong reactors in this population than controls, to increase the number of patients unnecessarily submitted to TB chemoprophylaxis (TISIURI et al., 2009; BASSUKAS et al. 2011).

Until today, the causal factors responsible for increasing the frequency of positive TST results observed in patients with psoriasis have not been defined. One of the hypotheses suggests the interference of the immunological activation of the Th17 and Th22 pathways by the disease (LIMA et al., 2011; KARATAS et al., 2016). However, there are no studies that have evaluated the relationship between TT outcome and levels of cytokines involved in pathways common to psoriasis and tuberculosis.

It has been suggested that the interferon-γ (IGRA) release assay should replace the use of TST in the TBLI screening because it has greater sensitivity and specificity (BELO et al., 2014). However, the studies comparing patients with psoriasis and normal controls observed a lower concordance of TST(LAFFITTE et al, 2009; LIMA, 2013). It was then questioned whether the reason was the interference of the disease itself (LAFFITTE et al., 2009; DE ANDRADE LIMA et al., 2011), immunosuppression (BARTALEZZI et al, 2009; RAMOS et al., 2013, CONSTANTINO et al., 2013, HELWIG et al, 2012; CHIU, HSUEH, TSAI, 2011) or epidemiological factors such as age (TAVAST et al., 2012), contact with cattle ((RAMOS *et* *al*, 2013; LAFFITTE *et* *al*, 2009)) or vaccination with the Bacilli of Calmette-Guérin (SAUZULLO *et al*., 2013; LAFFITTE *et* *al*, 2009).

The test possibly affected by immunosuppression is also controversial. Some studies have found that immunosuppression affects the results of IGRA (BERTALEZZI et al, 2009, RAMOS et al, 2013, CONSTANTINO et al, 2013, HELWIG et al, 2012) while others the TS T (TAVAST et al., 2012) and there are still those that did not find an influence on both tests (MARTYN-SIMMONS et al., 2012; LATORRE et al., 2014). As many patients with psoriasis are screened for TBLI using an immunosuppressant, more often methotrexate (MTX) (DAUDÉN et al., 2016), it becomes important to elucidate whether immunosuppression interferes with TBLI screening tests.

There are several reasons why the issue has not been elucidated. Most studies evaluating the effect of immunosuppression are retrospective and present factors that may influence test results (CONSTANTINO et al 2013, RAMOS et al, 2013) as individuals with varied diseases, heterogeneous BCG vaccination status and geographic region of origin. (BARTALEZZI et al, 2009, TAVAST et al, 2012, RAMOS et al, 2013).

The search for an association between the results of screening tests with factors that could infer the impact of immunosuppression such as the degree of clinical control, variation in the inflammatory and immunological markers received little attention so far. Sauzullo et al. (2013) described in-vitro a reduction in the levels of interferon-gamma (IFN-γ) specific for TB inversely proportional to levels of a tumor necrosis factor alpha blocking drug.

Regarding the inflammatory activity, Constantino et al. (2013) found an association between undetermined IGRA and high levels of C-reactive protein (CRP) in rheumatoid arthritis, with no similar evaluation for psoriasis. The relationship of the tests with the clinical activity of the disease measured by the variation in the PASI (psoriasis area and severity index) score has not been evaluated to date.

Therefore, this study aims to compare the results of the IGRA and TST tests before and after immunosuppression with methotrexate in patients with psoriasis, with the same BCG vaccination profile, from the same geographic region, and assessing whether there is an association of these results with the clinical and inflammatory activity of the disease.

The results of the study will help to better clarify the limitations and possible biases of tuberculosis screening tests in patients with psoriasis who live in places with a high likelihood of contact with tuberculosis.

#### Study goals and objectives

- 1. **Main objectives**

Verify-in patients with psoriasis, living in an endemic area for tuberculosis and vaccinated with BCG, whether MTX significantly changes the frequency of TST and/or IGRA results and concordance between tests and whether positive tests are associated with age, disease duration in years, blood glucose, body mass index (BMI), PASI (psoriasis area and severity index), CRP, erythrocyte sedimentation rate (ESR), TNF-α, IFN-γ, IL-12, IL17 and IL 23 before and after the use of methotrexate for 12 weeks and PASI reduction after treatment.

- 1. **Specifics objectives**

Determining before and after 12 weeks of methotrexate use in psoriasis patients:

- The value of PASI
- The PASI reduction percentage
- Frequency of QuantiFERON negative, positive, indeterminate, and the test agreement.
- The TST results in mm and the test agreement.
- The agreement between TST and QuantiFERON
- The values ​​and means of the inflammatory tests (ESR and CRP)
- The levels of cytokines; TNF-α, IFN-γ, IL-12, IL17, and IL 23.

Verify if after treatment with methotrexate if there is:

- Statistical difference in frequency of positive/negative/ indeterminates TST
- Statistical difference in frequency of positive/negative/indeterminate IGRA
- Statistical difference in frequency in the agreement between TST and IGRA
- Statistical difference in PASI, cytokines and inflammatory tests levels
- Association between positive and negative tests before and after treatment with sex, age, disease duration, weight, blood glucose, BMI, ESR, CRP, PASI, TNF-α, IFN-γ, IL-12, IL17 and IL 23, absolute PASI and Percentage reduction of PASI before and after treatment.
  1. **Secondary objectives**
- Characterize the clinic and demographic characteristics of the sample following the variables sex, age, weight, BMI, disease duration in years, diabetes, associated psoriasis forms: geographical tongue, palmoplantar psoriasis, psoriasis of the scalp, inverted psoriasis, nail psoriasis, place of residence (urban or rural), contact with cattle, alcohol intake, smoking, prior contact with a tuberculosis carrier, chest X-ray abnormality suggestive of TBLI,
- Verify the association between the sustainer status with sex, age categorized, disease duration, weight, BMI, alcohol consumption, smoking, presence of other forms of psoriasis associated, blood glucose (normal, diabetic), serum levels of INF-γ, TNF-α, interleukin-12, interleukin-17, interleukin-23, ESR, CPR. The association with ESR, CPR, and cytokines will be verified before and after treatment. The variables presenting p < 0.05 will be considered a positive association.

#### Study Design

This will be a prospective, single-arm, self-controlled, quasi-experimental study associated with a cohort.

Follow-up

#### 3.1 Study period

| *Phase/year* | ***2014*** | ***2015*** | ***2016*** | ***2017*** | ***2018*** |
| --- | --- | --- | --- | --- | --- |
| Scientific project | X |  |  |  |  |
| Ethics committee submission |  | X |  |  |  |
| Data collection and follow up* |  | X** | X | X | X |
| Laboratory analysis |  |  |  | X |  |
| Data analysis |  |  |  | X | X |
| Manufacture of scientific articles |  |  |  |  | X |

* The deadline for the final analysis of data from the follow-up period will be February 2018.

* * The Collection can only be initiated after approval by the ethics committee.

3.2 Sampling type and sample size definition

The sample will be systematic random.

It will be included sequentially patients over 18 years of age with moderate to severe plaque psoriasis with the indication of methotrexate referred by dermatologists to initiate the follow-up in the outpatient clinics of the Hospital of the Federal University of Pernambuco who meet the eligibility criteria and sign the consent form.

The sample size calculation was performed considering the effect of MTX on PASI. The calculation used the formula for comparing paired differences.

To achieve a power of 80 % and a level of significance of 5 % (two-sided) for detecting an effect size of 0,65 between pair was necessary 22 pairs.

For the other variables, the objective was to verify if this effect produced on the PASI would be sufficient to produce a change in them.

#### 3.3 Eligibility criteria

***Inclusion criteria*** :

Patients over 18 years of age with moderate to severe plaque psoriasis with the indication of methotrexate referred by dermatologists to initiate the follow-up in the outpatient clinics of the Hospital of the Federal University of Pernambuco.

***Exclusion criteria:***

Absence of BCG vaccination scar, pregnant women, women breastfeeding, previous use of systemic treatment, previous use of immunosuppressants, use of topical medications for psoriasis in the last 6 months, use of drugs aggravating of psoriasis, personal history, signs or symptoms of tuberculosis, chest X-ray compatible with lung disease other than latent tuberculosis, previous malignancy, positive serology for HIV, hepatitis B or C, and liver enzyme elevation, renal clearance less than 60 ml/min, lymphopenia below 1500 lymphocytes, platelet count below 100,000, or leukopenia below 3500 leukocytes.

#### Methods of collection

#### Collection protocol

**Evaluation visit**

Patients who meet the inclusion criteria will be invited to participate in the research. The patient will only initiate the research protocol after signing the “Free and Informed Consent Term” (Appendix 1). After signing the consent form, the main researcher will collect the demographic data by interview and identification document. The data will include the date of birth, current age, comorbidities, and current medications in use (Appendix 2).

Next, the presence of the BCG vaccine scar will be checked. In the absence of the scar, the patient will be excluded. In the presence of BCG vaccine scar, other exclusion criteria will be verified; current or less than six months use of topical treatment for psoriasis and current or previous systemic treatment for psoriasis (Appendix 2). A standardized questionnaire will be used to assess the presence of active TB (Appendix 3) In the case of a positive response to any active TB symptom, history of TB treatment, or history of TB prophylaxis the patient will be excluded.

After the interview, the patients will be scheduled for collection of exams in the laboratory of the hospital of the UFPE clinics tree days before the visit one. These will include complete blood count, liver enzymes, renal function, serology of hepatitis B, C, HIV, erythrocyte sedimentation rate, quantitative C- reactive protein, rheumatoid factor, and pregnancy test for women. The chest X-ray will be performed in the radiology department of the hospital.

**Visit one**

The first visit will be done following the following protocol:

1. The main research will check the laboratory results of tests and the chest *x*-ray report. The results will be noted on the Clinical Data Record (Appendix 2) and in Laboratory follow-up Record (Appendix 4). In the case of contraindications to MTX or pulmonary radiological changes not due to possible LTBI, the patient will be excluded. The result of fasting blood glucose will be noted in mg/dl (Appendix 4).
2. The physical examination will be performed by the main research to check the severity and associated forms of psoriasis. It will be verified the presence of geographic tongue, nail psoriasis, inverted psoriasis, palm-plantar psoriasis, and scalp psoriasis. The severity of psoriasis will be quantified by the PASI score (Appendix 5)
3. The laboratory tests will be realized by *[name]*. The blood will be obtained by direct venipuncture in appropriate tubes. For the QuantiFERON-TB Gold test, one milliliter of blood will be collected in each of three tubes separately according to the sequence in the manufacturer's instructions (Cellestis, Melbourne, Australia). For the IFN-γ and TNF-α tests, 3 ml of blood will be collected in a tube with citrate. The blood samples will be identified with the inscription “Sample 1”, date, hour, and research number.
4. The blood samples will be immediately forwarded to the respective laboratories by the main research in a Styrofoam box. First, the samples for cytokines will be sent to the Laboratory of Immunopathology Keizo Asami-LIKA under the responsibility of [name]. Second, the IGRA will be sent to the laboratory of Immunoepidemiology, Department of Immunology, Aggeu Magalhães Research Center (CPqAM) -Fiocruz under the responsibility of [name].
5. After the collection of blood, TST will be performed by *[name]* using the Mantoux technique described above.

**TST reading visit one**

1. The patient will be scheduled to read the result of the TST in 72 hours. The TST reading will be performed by *[name]*. The results will be photographed for archiving and noted in the laboratory data record. (Appendix 6).
2. The main research will provide the MTX prescription. The patients will be instructed to take 3 cp of 2.5 mg of MTX twice in a single day of the week, for a total dose of 15 mg per week without dose progression. Patients should start the medication the next day to avoid errors. They will be instructed to intake 5 mg of folic acid once a week in the day after the use of MTX.
3. Patients will reevaluated 30 days after starting medication to assess adverse effects. In case of adverse effects, they should attend the consultation before the deadline. Patients who discontinued the medication or skipped doses for any reason before the second visit were excluded.
4. The patient will be scheduled with one month and with tree months, before visit two, to verify the adherence to methotrexate and perform blood count, liver enzymes, renal function, and pregnancy test for women. The CPR and ESR levels will be reassessed only in three months. In case of a change in the exams or if the patient stops MTX, they will be excluded.

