**|Visit two**

1. The main research will check the laboratory results of tests. The results will be noted in the clinical evaluation and laboratory records. In the case of laboratory abnormalities that contraindicate the MTX, the patient will be excluded. The result of fasting blood glucose will be reassessed to verify if it meets the criteria for diabetes.
2. The physical examination will be performed to reassess the severity of psoriasis by the PASI score with the methodology described previously.
3. The blood collection and TST application will be performed by *[name]* using the Mantoux technique. The samples will be identified with the inscription “Sample 2”, date, hour, and research number.
4. The sample will be delivered to forwarded to the respective laboratories immediately after collection, will be centrifuged, and incubated in a maximum of 1 hour. The samples from visits 1 and 2 will be stored in different trays after freezing.

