#### Data analysis plan

The IBM Statistical Package version 23.0 (IBM corp., Armonk, NY) will be used for the statistical calculations.

- Data will be analyzed descriptively through statistical measures: mean ± standard deviation or median and percentiles for numerical variables and absolute and percentage frequencies for categorical variables.
- It will be verified whether there is a significant change in the results of TST and/or IGRA tests, with 2 or 3 categories, classified according to the variables descriptions by the McNemar test. A P < 0,05 will be considered significant.
- It will be verified whether the difference in the comparison of test results is significant before and/ or after treatment by the McNemar test. A P < 0,05 will be considered significant.
- The agreement between each and between the IGRA and the TST before and after treatment, with two or three categories, will be verified by the Cohen’s kappa.
- For numeric continuous variables, the normality will be tested using the Shapiro-Wilk test. To compare the mean of paired continuous variables will be used the Student's t-test for paired variables for variables with a normal distribution, and the Wilcoxon test for variables with a non-normal distribution.
- To compare the TST and IGRA results with the means of numerical continuous variables will be used the Student's t-test for variables with a normal distribution, and the Mann-Whitney test for variables with a non-normal distribution.
- Will be verified the association between the sustainers or non-sustainers status with the categorized variables by the Fisher Exact test. The variables presenting p < 0.05 will be considered a positive association. The variables will be sex, age categorized, duration of illness categorized, alcohol consumption, smoking, presence of other forms of psoriasis associated, blood glucose (normal, diabetic).
- The association between the sustainers or non-sustainers status with the medians/medians of the continuous variables will be verified by t-Student test or Mann-Whitney test, The variables will be the age in years, disease duration in years, BMI, blood glucose in mg/dl, serum levels of INF-γ, TNF-α, interleukin-12, interleukin-17, interleukin-23, ESR, CPR. The association with ESR, CPR, and cytokines will be verified before and after treatment.
- The variables presenting p < 0.05 will be considered a positive association.

.

1. ***Budget****

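### Patients are excluded for stopping, missed doses or laboratory changes after methotrexate starts, so the before-after results describe only adherent patients who tolerated the drug

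*Protocol*

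**What the plan says.** Three rules in Protocol section 4.1 act after treatment has begun.

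- TST reading visit one, item 3: "Patients who discontinued the medication or skipped doses for any reason before the second visit were excluded".
- TST reading visit one, item 4, on the checks at one and three months (blood count, liver enzymes, renal function, pregnancy test): "In case of a change in the exams or if the patient stops MTX, they will be excluded". No threshold is given.
- Visit two, item 1: "In the case of laboratory abnormalities that contraindicate the MTX, the patient will be excluded". The PASI follows in item 2, and the blood draw and TST in item 3.

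These rules are separate from the eligibility criteria in section 3.3. The main objective asks "whether MTX significantly changes the frequency of TST and/or IGRA results and concordance between tests", with measurements "before and after the use of methotrexate for 12 weeks and PASI reduction after treatment". On design: "This will be a prospective, single-arm, self-controlled, quasi-experimental study associated with a cohort". The Data analysis plan compares TST and IGRA results "classified according to the variables descriptions by the McNemar test". For continuous variables it states: "To compare the mean of paired continuous variables will be used the Student's t-test for paired variables", with the Wilcoxon test where the distribution is not normal. All of these need a result from both visits. No section plans visit-two measurements in excluded patients.

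**The concern.** An exclusion made before treatment defines the population. An exclusion made after treatment starts can depend on what the treatment did. Stopping for adverse effects, and laboratory abnormalities that arise under MTX, are possible consequences of the drug whose effect is being measured. Removing these patients before the second TST, QuantiFERON, cytokine and PASI assessment selects the sample on the treatment's own effects. In a single-arm study no comparison group can reveal or offset that selection.

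The clearest case is visit two. A patient may have taken every dose for 12 weeks, which is exactly the exposure named in the main objective, and still be removed on the laboratory check that precedes the measurements.

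The sustainer analysis is affected too. Section 4.2 defines non-sustainers as patients who did not reach a 50% PASI reduction, or who reached it and later lost it. It does not say where a patient excluded before the week-12 PASI belongs.

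**Working it through.** **1. The plan's own figure.** Section 3.2 gives 22 pairs for an effect size of 0.65, 80% power and 5% two-sided significance, based on PASI.

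- Normal approximation: (z0.975 + z0.80)² / 0.65² = 18.6, so 19 pairs.
- Exact paired t-test: 21 pairs (power 80.9%); at 22 pairs the power is 82.8%.
- Wilcoxon adjustment: 21 / 0.955 = 21.99, so 22 pairs.

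The 22 reproduces. It counts complete pairs, and no allowance for exclusions is stated.

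**2. Effect on numbers (exclusion rates assumed; none are given).** Starters needed for 22 pairs = 22 / (1 − d). The last two columns take the case where only 22 start.

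| Excluded, d | Starters needed | Pairs left of 22 | Power at 0.65 |
|---|---|---|---|
| 5% | 24 | 21 | 80.9% |
| 10% | 25 | 20 | 78.7% |
| 20% | 28 | 18 | 73.9% |
| 30% | 32 | 15 | 64.9% |

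The missed-dose rule alone could produce such rates. MTX is taken on one day a week, so there are 12 dosing days in 12 weeks. With an assumed, independent chance w of missing each one, the share excluded is 1 − (1 − w)^12: 11.4%, 21.5% or 30.6% for w = 1%, 2% or 3%. Recruiting more patients restores power but does not remove the selection.

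**3. PASI, assumed worst case.** Suppose 15 of 22 completers reach a 50% reduction, and 3, 6 or 9 excluded starters are all non-responders.

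- Completers: 15/22 = 68.2%
- 15/25 = 60.0%, a fall of 8.2 points, or 2.7 per excluded patient
- 15/28 = 53.6%, a fall of 14.6 points, or 2.4 per excluded patient
- 15/31 = 48.4%, a fall of 19.8 points, or 2.2 per excluded patient

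**4. TST/IGRA: the direction is open.** Rate in all starters = (1 − e) × rate in completers + e × rate in excluded. Assume 20% are excluded and a test result changes in 10% of completers.

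- Excluded patients change more often (50%): 0.8 × 10% + 0.2 × 50% = 18%. The study's 10% is too low.
- Excluded patients had little exposure and never change (0%): 0.8 × 10% + 0.2 × 0% = 8%. The study's 10% is too high.

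The documents give no basis for choosing between these.

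**5. The two laboratory rules.** Item 4 under TST reading visit one covers the three-month check made before visit two. Item 1 of visit two then has the investigator review the laboratory results. The first rule excludes on a change of any kind. The second excludes only on abnormalities that contraindicate MTX. The same results can therefore be judged by two different criteria.

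**The case against.** The strongest counter-argument is that an adherent-patient question is legitimate. The objective concerns 12 weeks of MTX use, and the rationale concerns patients screened while on an immunosuppressant. A week-12 test in someone who stopped in week 3 does not answer that, and including such patients dilutes exposure. This stands for patients who stopped early or missed doses: an adherent set is a valid analysis if it is labelled as one. It does not cover patients removed on laboratory grounds at visit two, who have had the full exposure.

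It can also be said that analysis sets belong in a statistical analysis plan. That is so, but the protocol decides which measurements are taken, and an analysis plan cannot supply data that were never collected.

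Several stronger readings are tempting and are not supported:

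- **The TST/IGRA effect is biased towards no change because the most affected patients are removed.** This may apply to the laboratory and toxicity exclusions. Patients who missed doses are the less exposed, and removing them can act the other way. The protocol does not name blood counts as a marker of immunosuppression, and it gives no link between liver, renal or pregnancy tests and TST/IGRA.
- **Any changed laboratory result excludes.** That is the literal sense of item 4, but the visit-two rule is narrower.
- **Each removed patient is worth 1/22 = 4.5 percentage points.** That is the weight of an included patient. The worst case above gives 2.2 to 2.7 points.
- **The sustainer share is overstated.** The plan sets out associations with sustainer status, not an estimate of the share. The non-sustainer wording could also be read to cover someone who stops for lack of effect.

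**Conclusion.** The point holds in limited form. The rules select on events after treatment starts. The laboratory and toxicity exclusions select on consequences of treatment and, at visit two, can remove fully exposed patients just before the second measurement. The results then apply to adherent patients who tolerated MTX, and the protocol does not say so. For TST/IGRA neither the sign nor the size of any bias can be derived from the documents. For PASI, the fall from 68% to between 60% and 48% is a worst case: the 15/22 response, the 3 to 9 exclusions and the absence of any response among those excluded are all assumptions. The defect should be corrected before the data are used to describe what MTX does to the tests in patients who start it.

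**What to change.** Separate the clinical decision on MTX, which is not addressed here, from leaving the study's measurements and analysis.

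1. Reconcile the laboratory wording of item 4 under TST reading visit one with item 1 of visit two.
2. State that patients who reach visit two after 12 weeks of exposure have the planned PASI, blood draw and TST, and stay in the before-after analysis whatever their visit-two laboratory results.
3. For patients who stopped or missed doses, obtain the planned week-12 assessments where clinically appropriate, and record the doses taken.
4. Report results for all starters with a week-12 test and for the fully adherent set. Label the latter as applying to adherent patients only.
5. State explicitly how patients who stop before week 12 are classified in the sustainer analysis.
6. Report the number of exclusions and the reasons for them.

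The cost is mostly protocol wording, plus some dilution from short exposure, which the adherent-set analysis will show. A few more test kits are needed. The budget lists 100 QuantiFERON tubes; at 3 tubes per visit and 2 visits that is 100 / 6, or 16 complete patients, if that line is the whole supply. Tube numbers would therefore need checking.
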